**Motor**						
Motor reserve	PASE	Physical Activity Scale for the Elderly (PASE)	Washburn et al. [102]	X		
Physical activity	IPAQ	International Physical Activity Questionnaire (IPAQ)	Craig et al. [70], Lee et al. [71]	X	X	X
PD motor symptoms	MDS-UPDRS-III	Movement Disorder Society Unified Parkinson’s Disease Rating Scale Part III	Goetz et al. [103]	X	X	X
Dual tasking	TuG	Timed Up and Go Test—Single and Dual Task Condition	Podsiadlo and Richardson [104], Zirek et al. [105]	X	X	X
Fine motor skills	PPT	Purdue Pegboard Test	Tiffin and Asher [106], Agnew et al. [107]	X	X	X
**Sleep**						
Subjective sleep quality	PDSS	Parkinson’s Disease Sleep Scale	Trenkwalder et al. [108]	X	X	X
RBD symptom severity	RBDSQ	REM sleep behavior disorder screening questionnaire	Stiasny‐Kolster et al. [109]	X		
	RBD-I	Innsbruck REM sleep behavior disorder inventory	Frauscher et al. [110]	X		

The motor examination with the motor part of the Movement Disorder Society (MDS) Unified Parkinson’s Disease Rating Scale (MDS-UPDRS-III) will be conducted and videotaped by outcome assessors and rated by one of two movement disorder specialists blinded for the diagnostic group (HC vs. RBD), experimental group allocation (early intervention group vs. delayed-start group) and time point of assessment (t0, t1, t2, t3, t4). The same movement disorder specialist will rate all videos of one subject. Ten randomly selected videos of the first 100 MDS-UPDRS-III recordings were double-rated by the two movement disorder specialists and the MDS-UPDRS-III total score reached an intraclass correlation (ICC) of 0.87, indicating good to excellent interrater reliability. Rigidity assessments as part of the UPDRS-III are conducted and rated during the test sessions by the outcome assessors. All outcome assessors are previously trained by the movement disorder specialists.

#### Feasibility

As this clinical trial constitutes one of the first non-pharmacological intervention studies for individuals with iRBD, the feasibility assessment of such an intervention is of great interest. We will report the participation score, i.e., the proportion of individuals of the continuously expanding Cologne iRBD cohort willing to participate in the intervention study (regardless of subsequent randomization). Additionally, within the intervention study, factors of interest include adherence to the intervention protocol (compliance) in terms of the rate of successful completion of the cognitive training protocol operationalized as the completion of at least 80% of planned training sessions, equivalent to a minimum of 12 training sessions, and the consistent utilization of the digital activity diary. Furthermore, the overall dropout rate across data collection time points will be compared between the early intervention group and the delayed-start control group. While the study does not incorporate a systematic collection of qualitative feedback, participants are encouraged to provide feedback on the cognitive training and activity diary and communicate any technical challenges they encounter to their designated contact person throughout the study.

#### Accelerometry: physical activity tracking

All willing participants will be asked to wear a wrist-mounted movement sensor measuring linear acceleration and angular velocity on their dominant hand for 7 days around each assessment time point. The sensors will be distributed either during the assessment session (along with a prepaid return envelope) or sent to the participants 10 days prior the next assessment. The participants will be instructed to wear the sensor as much as possible throughout their days and nights. Additionally, participants will be asked to fill out a diary noting their bedtimes, daily activities, and periods when they are not wearing the device.

The CE-certified movement sensor used in this study is the AX6 from Axivity Ltd, Newcastle upon Tyne, England. Detailed information about the AX6 and the wrist strap can be found in the Data Sheet documents available on the Axivity website (https://axivity.com/product/ax6). The sensors will be configured to record data continuously for 7 consecutive days and nights (168 h) at a sampling rate of 100 Hz with an accelerometer range of ± 8 g. Sensor set-up and data storage will be managed using the open source AX3/AX6 OMGUI Configuration and Analysis Tool (https://github.com/digitalinteraction/openmovement/wiki/AX3-GUI). Data retrieval from the sensor is only possible via a USB cable connection. Data will be saved in the Continuous Wave Accelerometer (*.cwa) binary format containing the raw actigraphy data, metadata, and device configurations.

#### Magnetic resonance imaging

Extensive brain imaging with a 3 T SIEMENS PRISMA scanner equipped with a 64-channel head coil will be conducted at the Research Center Jülich near Cologne for all willing participants at all time points (t0–t4). The MRI scanning will preferably occur within 7 days of the clinical and neuropsychological assessment. However, in case of technical difficulties with the scanner or timing issues with the participants (e.g., illness or personal reasons), it may be conducted up to 3 weeks apart. During MRI measurements, at least one member of the study team is present. This person will be supported either by another member of the study team or by a medical-technical radiology assistant of the Research Center Jülich. The net scanning time for all sequences lasts 69:33 min. The sequences, their features and specifications, spatial resolution, repetition times (TR), and echo times (TE) as the basic pulse sequence parameters are described in Table 2. The MRI data will be exported and saved in the DICOM format (*.dcm).

**Table 2 Tab2:** Magnetic resonance imaging protocol CogTrAiL-RBD

Sequence	Features	Duration
T1-weighted	The T1-weighted sequence will be used to monitor cortical thickness, gray matter volume, and deformation. These metrics are well-established markers which might change upon training. Sequence parameters: 0.9 mm isotropic MP2RAGE, TR 2500.0 ms, TE 2.22 ms	6:24 min
Neuromelanin-sensitive turbo spin echo	Turbo spin-echo (TSE) sequences allow for contrast evaluation of neuromelanin containing structures, i.e., locus coeruleus and substantia nigra. Measures of locus coeruleus integrity like volume, voxels with highest intensity as well as contrasts of spatial subdivisions will be performed [111]. Such measures will elucidate the role of an intact locus coeruleus as prerequisite for successful cognitive training. Sequence parameters: 0.4 × 0.4 × 1.8 mm^3^ resolution, TR 825.0 ms, TE 18.00 ms	7 × 2:24 min = 16:48 min
Multi-shell diffusion	We will analyze metrics of white and gray matter microstructure obtained via modeling of the measured multi-shell diffusion-weighted signal, including diffusion kurtosis imaging (DKI), neurite orientation dispersion and density imaging (NODDI), and free-water mapping [112]. Multi-shell diffusion additionally opens the possibility for advanced fiber tracking approaches allowing to disentangle complex fiber configurations (e.g., crossing fibers) [113]. These microstructural data were shown to correlate with motor and cognitive performance in PD and might be particularly sensitive to plastic changes of brain organization. Sequence parameters: 1.5 mm isotropic resolution, TR 3800.0 ms, TE 90.00 ms	6:32 min + 0:50 min + 0:50 min + 6:36 min + 4:07 min = 18:48 min
Task-based functional MRI	The Wisconsin Card Sorting Task will be applied during functional MRI (fMRI) as an established test engaging executive functions and working memory. We chose an established task including multiple cognitive domains to study broad effects of functional reorganization upon cognitive training. Due to the longitudinal study design, we will be able to monitor transitions of the activation pattern correlating to training effects and baseline cognitive capacity. To implement the Wisconsin Card Sorting Test (WCST) in the present study, the adapted version of the WCST [114] was further adapted for functional MRI measurements according to Lie et al. [115]. The WCST is programmed in Presentation®, Version 23, of NeuroBehavioral System Inc. Changes compared to the standard WCST include a fixed response time, which is necessary to create meaningful blocks for MRI analysis and ensure the same task duration for all participants. For presentation in the scanner using a mirror, the task is programmed in a mirror-reversed manner. Before conducting the task in the scanner, participants are asked to practice a brief version of the task on the experimenter’s computer to clarify any questions. The experiment randomizes both the order of target categories and the order of cards for each participant. Responses are made using key presses on the computer during the practice session and using a hand response device (Celeritas) in the scanner. To perform the task in the scanner, the keyboards need to be tested, and full visibility of the monitor through the mirror must be ensured. Sequence parameters: 2.0 mm isotropic resolution, TR 800.0 ms, TE 37.00 ms	12:28 min
Resting-state functional MRI	Resting-state fMRI is a highly established imaging modality to study functional connectivity of the brain. We will apply more advanced measures of dynamic functional connectivity, which we recently applied in patients with PD [116]. Sequence parameters: 2.0 mm isotropic resolution, TR 800.0 ms, TE 37.00 ms	10:20 min
Quantitative susceptibility mapping	Quantitative susceptibility mapping (QSM) measures cerebral iron content. QSM is susceptible for tissue changes in nigrostriatal dopaminergic pathways [117]. Sequence parameters: 0.9 mm isotropic resolution, TR 47.0 ms, TE1 7.38 ms, TE2 14.76 ms, TE3 22.14 ms, TE4 29.52 ms, TE5 35.76 ms, TE6 42.00 ms	4:45 min
	Total net scanning time	69:33 min

*MRI* magnetic resonance imaging, *TE* echo time, *TR* repetition time

#### Polysomnography

All participants with iRBD undergoing MRI will also be invited to participate in two polysomnography sessions during their (first) period of cognitive training. For participants in the early intervention group, the polysomnography sessions will take place between t0 and t1, while for participants in the delayed-start control group, the sessions will occur between t2 and t3. The first polysomnography session will be conducted before the start of cognitive training, and the second session will be held in the last or second-to-last week of training, following a training day. The participants’ sleep prior to and during cognitive training will be monitored using mobile polysomnography equipment including 10 EEG channels, electromyography (EMG) of the chin, arms, and legs, surveillance of breathing efforts, as well as high-definition infrared (IR) videorecording. The SOMNOscreen plus device from SOMNOMedics GmbH, located in Randersacker, Germany, will be utilized.

The mobile nature of the polysomnography device allows for examinations to be conducted in the participants’ homes or hotel rooms, providing high convenience for the subjects. All participants are already familiar with the polysomnography examination from their iRBD diagnostic process, minimizing first-night effects. The polysomnography set-up takes approximately 90 min. After completing the set-up, participants can freely move as there are no cables restricting movement and they can spend their evening to their liking and go to bed at their preferred time. The following morning, a member of the study team will detach the polysomnography equipment. The polysomnography data will be saved in the proprietary file format of SOMNOMedics GmbH, which can be converted to the European Data Format EDF + format (*.edf), which is commonly used to store multichannel medical time series data.

### Data management and monitoring

All collected data will be pseudonymized with an individual identification number following the format RBD-XXX for individuals with RBD and HC-RBD-XXX for HC individuals, where XXX represents a non-consecutive, randomly generated three-digit number. Paper-based data such as the scoring sheets of the clinical and neuropsychological assessments will be stored in lockable cabinets in a room with restricted access at the University Hospital Cologne, sorted by participant ID for easy access at each stage of the study. Data acquired on paper will be digitalized by one staff member and double-checked by another. The progress of data collection, scoring, digitalization, and monitoring will be documented. Prior to data analysis, range checks for data values will be conducted. All digitally acquired data, such as questionnaire data from SoSci Survey (SoSci Survey GmbH, Munich, Germany), the MDS-UPDRS-III videos, the accelerometry module (*.cwa files), and the PSG module (proprietary file format and *.edf files), will be saved on a secure server of the University Hospital Cologne with restricted access only to the staff involved in this project. The MRI data (*.dcm files) is sent to a Picture Archiving and Communication System (PACS) and stored in the study archive of the Research Center Jülich in a data protection-compliant and pseudonymized manner. Spreadsheets concerning sensitive data, such as the name-ID key list, names, and contact information, will be further protected by a password and saved on a secure server with access only to the staff involved in participant management of the study. Additionally, all digitally acquired data will be backed-up on an encrypted hard drive stored in a lockable cabinet in a room with restricted access at the University Hospital Cologne. Following good scientific practice, data will be stored for at least 10 years. The final data set can be accessed by the study contributors at the University Hospital Cologne and the Research Center Jülich. Participants will also be requested to authorize the research team to share the pseudonymized data with members of other research groups from university and non-university research institutions for in-depth data analysis within non-commercial research projects. This study does not involve the collection or storage of biological samples. Auditing is done on a monthly basis for internal reasons, a yearly report is sent to the sponsor.

### Expected harms and adverse events monitoring

During the execution of clinical and neuropsychological assessments, accelerometry, cognitive training, and the healthy, active lifestyle module, we expect no risks or complications and subsequent issues, except for mild transient fatigue. The MRI is a non-invasive procedure for functional and structural imaging of tissues, utilizing strong magnetic fields and high-frequency radio waves without involving radioactively labeled ligands or X-rays. To minimize the risk of any MRI-related complications, the detailed medical history of participants is assessed to determine their MRI eligibility. Prior to scanning, participants are asked to remove all metallic objects and empty their pockets. Under careful consideration of inclusion and exclusion criteria, no known health risk exists for patients undergoing MRI. Experienced specialist physicians in (neuro-)radiology evaluate every MRI scan diagnostically about incidental findings. If any need for further medical measures arises from the review of the MRI examination, the study physician will inform and support the participants accordingly upon their request. All participants are informed about the possibility of incidental findings and their medical, legal, insurance-related, and psychological consequences. The burden on the participants from the mobile polysomnography is considered low since the individuals with iRBD are familiar with the procedure from the diagnostic process. The surface electrodes are applied similarly to adhesive patches and participants can sleep in their familiar environment or a similar setting (e.g., a hotel room). Some participants may report a mild to moderate sensation of foreign objects.

Overall, under careful consideration of the inclusion and exclusion criteria, the risks of the study are minimal. Participants will be informed about possible risks and adverse events (AE) at their t0 visit. Participants can withdraw from the study at any point without providing a reason and without facing any disadvantages. No written explanation is required, and a verbal statement is sufficient for dropout. Outcome assessors and study coordinators will be instructed to monitor and document all AE throughout the study. If a serious AE occurs, the study physician will be consulted and asked to assess whether or not a causal relationship with the intervention is considered possible. Beyond the trial, participants will be part of the local iRBD cohort, receiving access to approximately yearly clinical visits and additional visits as needed.

### Statistical analyses

In the present study protocol, we will report the statistical analyses for the primary and secondary outcomes of the neuropsychological and motor assessments in the first parallel-group phase of the randomized controlled trial. Separate analysis plans for the exploratory outcomes physical activity measured by accelerometry, brain imaging parameters, and polysomnography and exploratory analyses (e.g., subgroups) will be preregistered in the Open Science Framework (OSF, https://osf.io/). The statistical analyses will be conducted after the last t2 visit of the last participant. Data preprocessing, statistical analyses, and data visualization will be conducted in R [118] with commonly used statistical libraries, e.g., dplyr, lme4, and ggplot2.

For the baseline comparisons between the early intervention group and the delayed-start control group, independent sample *t*-tests, Wilcoxon rank-sum tests, or χ^2^ tests will used as appropriate. Variables and test scores will be previously inspected for normal distribution by Shapiro–Wilk tests. As effect sizes, Cohen’s *d* will be reported for *t*-tests and *r* for Wilcoxon rank-sum tests, indicating small (*d* ≥ 0.2; *r* ≥ 0.1), moderate (*d* ≥ 0.5; *r* ≥ 0.3), or strong (*d* ≥ 0.8; *r* ≥ 0.5) effects.

For the analysis of training effects in the primary and secondary outcomes, linear mixed effects (LME) models will be used. Dependent variables are the respective primary or secondary outcome measures. All dependent variables are assessed at three points of time. The LME models include time (t0, t1, t2), group (early intervention group and delayed-start control group), and the interaction between time and group (time*group) as fixed factors. Furthermore, participants and time are included as random factors. Models will be estimated using the *lmer()* function of the *lme4*-package employing restricted maximum likelihood estimation [119]. Model fit will be evaluated using marginal *R*^2^, which considers the variance of the fixed effects only, and conditional *R*^2^, which accounts for both fixed and random effects. *t*-Tests will be conducted to assess the significance of single coefficients. For the interaction effects, relative effect sizes with 95% confidence intervals will be reported and defined as the difference of the mean change over time in the early intervention group minus mean change over time in the delayed-start control group divided by the pooled baseline standard deviation of the cohort. Within the analysis of training effects, we will pursue an intention-to-treat approach. No imputation methods will be used, as one strength of LME models is their ability to deal with unbalanced designs, for example, due to missing values in longitudinal data.

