### Sample size and power calculation

To determine an adequate sample size, an a priori power analysis was conducted with G*Power [57] (http://www.gpower.hhu.de). The study will be powered to reliably detect behavioral effects in the domain of executive functions (the primary outcome) in the first parallel-group phase of the randomized controlled trial in individuals with iRBD. According to two meta-analyses on cognitive training in healthy older adults [58] and individuals with PD [36], we expect a medium effect size (Cohen’s *d* = 0.5) in the domain of executive functions. With a two-sided *α*-level of 0.05 and 80% power, the minimum sample size comparing the difference between two independent groups (allocation ratio 1:1) with a *t*-test is *N* = 128 (i.e., *n* = 64 per group).

We applied the correction formula of Borm et al. [59], acknowledging the increase of precision in estimating a treatment effect when the correlation between the outcome measure at baseline and retest ($$\rho$$) by ANCOVA is considered: *n*_cor_ = *n**$$\sqrt{1-{\rho }^{2}}$$. A meta-analysis [60] on the reliability of neuropsychological measures identified particularly high correlations between baseline and retest measures of executive functions (Pearson’s *r* ≥ 0.80). Following, the G*Power estimate of *n* = 64 per group was corrected by the factor $$\sqrt{1-{0.8}^{2}}=0.6$$, resulting in a minimum sample size of *n*_cor_ = 38 per group, i.e., a total sample of *N*_cor_ = 76. The estimated dropout rate for the first parallel-group phase of the randomized controlled trial of the present trial is 5%, based on previous experiences with a similar intervention in individuals with PD [61]. Following, we aim to recruit *N* = 80 (= 76/0.95) individuals with iRBD for the present trial.

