### Randomization and blinding

Randomization in CogTrAiL-RBD is based on a minimization procedure designed to minimize differences between the early intervention group and the delayed-start control group in age, sex, and premorbid IQ [63]. The minimization randomization is implemented using the R package *Minirand* [64]. We aim at a 1:1 ratio of the number of subjects in the early intervention group and the delayed-start control group. The covariates age, sex, and premorbid IQ will be equally weighted (1/3 each). The participants with iRBD will be consecutively randomized following the clinical and neuropsychological t0 baseline assessment by a person not involved in t1 to t4 data collection, preferably by their individual contact person, who will assign the participants to the intervention and monitor their training progress.

The assessments will be double-blinded at t0 baseline (i.e., randomization will be carried out after the t0 baseline assessment) and single-blinded at t1 to t4 posttests and follow-ups (i.e., outcome assessors do not know the participant’s group allocation). Any violations of blinding will be documented, e.g., if participants do not fully comply with the explicit instruction not to give any clues about their experimental group allocation to the outcome assessors.

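### The sample size rests on ANCOVA baseline adjustment, but the planned mixed model gives a less precise change-score contrast; power at the stated inputs is still adequate

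*Protocol article*

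**What the plan says.** In the protocol article, Sample size and power calculation starts from a two-sample t-test with d = 0.5, two-sided α of 0.05 and 80% power, which gives 64 per group. It then applies a correction, "acknowledging the increase of precision in estimating a treatment effect when the correlation between the outcome measure at baseline and retest" is used through ANCOVA. The correlation comes from a meta-analysis that "identified particularly high correlations between baseline and retest measures of executive functions", stated as r ≥ 0.80. The figure of "64 per group was corrected by the factor" √(1−0.8²) = 0.6, giving 38 per group, 76 in total, and 80 after 5% dropout.

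Statistical analyses names no ANCOVA and no baseline covariate. For primary and secondary outcomes alike it fixes this model: "The LME models include time (t0, t1, t2), group (early intervention group and delayed-start control group), and the interaction between time and group". Participants and time are the random factors. The reported effect is the between-group difference in mean change, divided by the pooled baseline SD.

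Randomization and blinding states: "The assessments will be double-blinded at t0 baseline", because allocation takes place after that assessment. Minimisation uses age, sex and premorbid IQ, not the baseline executive score.

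**The concern.** The two sections describe different estimators. ANCOVA conditions on the baseline score. The planned model places that score in the outcome vector and estimates a separate group difference at t0, so its time-by-group terms compare mean changes. Since allocation follows the t0 assessment, the true group means at t0 are equal by design, and a free t0 difference spends information on a quantity known to be zero. For any ρ below 1 the change contrast is the less precise of the two.

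At stake are some avoidable loss of precision for the primary outcome, a larger loss for secondary outcomes whose baseline-retest correlation is lower, and a sample-size justification that does not describe the analysis to be run.

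**Working it through.** **Inputs**, all from Sample size and power calculation: d = 0.5, two-sided α = 0.05, power 80%, 1:1 allocation, ρ = 0.8, 64 per group before correction. The model comes from Statistical analyses. Assumptions: equal SD at all visits, equal correlation between visits, complete data, categorical time, random intercept.

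**Reproducing the plan.** The noncentral t calculation gives 64 per group (power 0.801). Then 64 × √(1−0.64) = 64 × 0.6 = 38.4, stated as 38; 2 × 38 = 76; 76/0.95 = 80. All the stated figures reproduce.

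**Variance factors**, relative to comparing follow-up means only:

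- ANCOVA, or a longitudinal model with equal t0 means: 1−ρ² = 1−0.64 = 0.36.
- Time-by-group interaction with free t0 means: 2(1−ρ) = 2 × 0.2 = 0.40.
- Ratio of the first to the second: (1+ρ)/2 = 0.90, so the constraint cuts the variance by (1−ρ)/2 = 10%.

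As a check, in three simulated data sets (38 per group, three visits, ρ = 0.8) a REML random-intercept model gave the same t1 interaction estimate as the raw difference in mean change, and a standard error matching the closed form. Over 20,000 replicates the empirical factors were 0.398 (change) and 0.363 (ANCOVA), and power for the interaction was 0.926.

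**The factor in the plan.** Required n is proportional to variance, so the ANCOVA multiplier on n is 1−ρ² = 0.36. The square root, 0.60, is the multiplier on the SD. At ρ = 0.8:

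| Basis | Factor on n | n per group for 80% power |
|---|---|---|
| Plan as written | 0.60 | 38 |
| Planned interaction (change contrast) | 0.40 | 27 (64 × 0.40 = 25.6, or 26, by simple scaling) |
| ANCOVA or equal t0 means | 0.36 | 24 |

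The planned contrast therefore needs fewer participants than the plan provides.

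**Power with 38 per group, d = 0.5** (noncentral t with effect d/√factor; 74 df for change, 73 df for ANCOVA). Only ρ = 0.8 comes from the document; the lower values are assumptions.

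| ρ | Change factor | ANCOVA factor | Power, change | Power, ANCOVA |
|---|---|---|---|---|
| 0.80 | 0.40 | 0.36 | 92.5% | 94.8% |
| 0.70 | 0.60 | 0.51 | 79.3% | 85.3% |
| 0.65 | 0.70 | 0.58 | 72.9% | 80.8% |
| 0.60 | 0.80 | 0.64 | 67.2% | 76.7% |

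The change factor equals the plan's 0.60 when 2(1−ρ) = 0.60, that is at ρ = 0.70.

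**Baseline imbalance.** Given an observed t0 difference, the change contrast is shifted by (1−ρ) times that difference. One standard error at 40 per group is √(2/40) = 0.22 SD, so the shift is 0.2 × 0.22 ≈ 0.045 SD at ρ = 0.8. The variance of this shift, in the same units, is (1−0.8)² = 0.04 = 0.40 − 0.36. It is the efficiency gap already counted above, seen conditionally on the imbalance.

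**The case against.** A reader might infer that the trial is underpowered, because it takes credit for a precision its model does not deliver. The document does not support that. The credit taken was a factor of 0.60, and the planned contrast delivers 0.40 at the stated ρ, with 92.5% power against a target of 80%. The powers at ρ = 0.6 to 0.7 do not show a shortfall either: the plan states r ≥ 0.80 and gives no lower value. It also gives no value specific to the five-test composite or to week 33, so a lower ρ is a sensitivity range only.

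A reader might also count regression to the mean as a second harm. Over randomisations the change contrast is unbiased, and the conditional shift is the same loss in another form. At 0.045 SD it is about a third of the contrast's own standard error, √(0.40 × 2/40) = 0.14 SD. Minimising on premorbid IQ may also reduce imbalance in the executive score somewhat.

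The other side can fairly add that a time-by-group mixed model with t0 as an outcome is valid and conventional, and that the plan's effect definition agrees with it. The random part is ambiguous too: a random slope or numeric time would change the contrast.

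All of this limits the size of the point. It leaves standing that the sample size cites one estimator and the analysis fixes another, less precise one, and that the better one needs no further data.

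**Conclusion.** The point holds as a mismatch with a modest cost. Under categorical time, a random intercept, equal SDs and complete data, the planned interaction has about 11% more variance than ANCOVA at ρ = 0.8 (0.40/0.36 = 1.11), which costs 2.3 percentage points of power (94.8 − 92.5). The trial is adequately powered at its stated inputs, because the misplaced square root errs on the safe side by more than this loss. Power below 80% with 38 per group would require ρ below about 0.70, which is an assumption.

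The loss grows as the correlation falls. The same model serves the secondary outcomes, for which no correlation is given; at an assumed ρ = 0.5 the variance would be a third higher than under ANCOVA (1.00 against 0.75). The change is worth making because it is nearly free, not because the present analysis is invalid.

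**What to change.** In Statistical analyses, constrain the t0 means to be equal: drop the group main effect and keep the group-by-t1 and group-by-t2 terms, with time as categorical. Alternatively, model t1 and t2 with the t0 score, interacted with time, as a covariate. Apply the same choice to the primary outcome and to every secondary outcome measured at t0, and state the random part exactly.

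In Sample size and power calculation, replace √(1−ρ²) by 1−ρ² as the multiplier on n, name the estimator that will actually be fitted, and present 38 per group as a margin over the corrected requirement of 24 (ANCOVA or equal t0 means).

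The cost is one change of model formula and a short correction to the text. No data are added, N stays at 80, and the change can be made before the analysis, which is scheduled after the last participant's t2 visit.
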